**Methods:**

In this multicenter randomized clinical trial, we will randomize between closed reduction followed by plaster casting and only plaster casting. Patients aged 18 to 75 years, presenting at the emergency department with a displaced distal radial fracture and requiring surgery according to the attending surgeon, are eligible for inclusion. Primary outcome is pain assessed with daily VAS scores from the visit to the emergency department until surgery. Secondary outcomes are function assessed by PRWHE, length of stay at the emergency department, length of surgery, return to work, patient satisfaction, and complications. A total of 134 patients will be included in this study with follow-up of 1 year.

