### Who will take informed consent? {26a}

Informed consent will be obtained by the attending physician at the emergency department. All physicians will be either trained in the protocol or supervised by someone who is.

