
**Fig. 1 Fig1:**
[figure not shown]
Power curve for simulation 1 assuming of balanced clusters (equal number of patients included per center)

However, in practice, unequal number of patients is expected to be included by each center. Also, seasonal effects should be accounted for in the analysis. Therefore, a second simulation was conducted in a similar way. The number of patients included per center was (roughly) based on the number of eligible patients in the past year (known for 4 hospitals) divided by 2 (assuming that 50% of eligible patients would participate). Inclusion rates for the two hospitals for which this was not known were set equal to the hospital with lowest inclusion rate, resulting in monthly inclusions of 13, 7, 7, 1, 1, 1. Seasonal effects were included by a monthly effect, which were assumed to follow a sine function with a period of 12 months. The SD of the seasonal effects over a 12-month period was set equal to the between cluster SD. The half period (*x* = *π*) was set equal to the moment of cross-over. For sample sizes varying from 60 (two months of inclusion) to 360 (12 months of inclusion), again 5000 simulations were run for each sample size considered. Linear mixed models were fitted including center as random effect and month and treatment as fixed effects. Using a two-sided alpha of 5%, *n* = 120 patients total (rounded to above) would be required in total to demonstrate non-inferiority with a power of 80% (Fig. 2). Accounting for a 10% loss to follow-up, a total of *n* = 134 patients will be included. It should be noted that in the simulations, it was assumed that only one VAS pain will be collected for each patient, while in reality multiple VAS scores (one per day) will be obtained during the period between the visit to the emergency department and the operation. An average VAS pain for each patient will be estimated by a multilevel linear mixed model using random intercept for patient nested within center. Including this aspect in the simulation studies was deemed too complicated, since no reliable estimates for the correlation between daily VAS pain scores in this setting are available. However, following the reasoning that multiple measures will lead to a more precise estimate than a single measure, it can be expected that in practice a higher power will be achieved compared to the simulations and including this is not strictly necessary (i.e., the simulations can be regarded as conservative in this respect).

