### Concealment mechanism {16b}

Since this trial will not be blinded, there are no concealment mechanisms. We use a simple algorithm to randomly pick A (closed reduction) or B (no closed reduction) six times and allocate treatment by order of hospital recruitment.

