### Implementation {16c}

The primary investigator generated the allocation sequence. Patients are enrolled by attending physicians in all participating hospitals. With the cluster randomization, every hospital will know beforehand what intervention to assign.

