## Data collection and management

### Plans for assessment and collection of outcomes {18a}

The primary outcome is the average of the pre-operative visual analog scale for pain (VAS) score, reported on daily basis from the ED visit until operation. The VAS score is an easy, valid, and reliable tool for pain measurement that has been widely used [32]. The VAS score will be presented as a horizontal line with in which the complete left side is defined as “no pain,” and the complete right side is defined as “the most extreme pain possible.” The patients will be asked to mark the position that corresponds with their pain experience. The VAS score prior and after the plaster application will represent their current pain experience. During the ED visit, patients will receive a “pain diary,” containing multiple empty VAS forms. Patients will be asked to report their average VAS score at the end of every day as well as the worst pain of that day (the latter will be used for a secondary analysis). The average will be calculated by adding all pain scores and dividing by the number of days for each patient. Besides the pre-operative VAS scores, they will also register the post-operative VAS score at 6 weeks and at 3, 6, and 12 months. The following parameters will serve as secondary outcome measures.

Average pain per day, average highest pain, and highest pain per day will all be analyzed to identify possible patterns secondary to the primary outcome of average pain from day 1 until surgery. The post-operative Patient-Rated Wrist Evaluation (PRWE) score [33] after 6 weeks and 3, 6, and 12 months will be assessed. The PRWE is a 15-item questionnaire designed to measure wrist pain and disability in activities of daily living. The PRWE allows patients to rate their levels of wrist pain and disability from 0 to 10 and consists of 2 subscales:Pain subscale: contains 5 items each of which is further rated from 1 to 10. The maximum score in this section is 50 and minimum 0Function subscale: contains total 10 items which are further divided into 2 sections, i.e., specific activities (having 6 items) and usual activities (having 4 items). The maximum score in this section is 50 and minimum 0

The length of stay in the ED will be measured in minutes and concerns the entire time that a patient is present in the ED. This will be calculated by subtracting the registration time from the discharge time.

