## Statistical methods

### Statistical methods for primary and secondary outcomes {20a}

Data for the primary outcome measure will be reported descriptively. Descriptive analysis will be performed in order to report outcome measures for the total population. Continuous data will be analyzed using an independent *t*-test or Mann–Whitney *U* test if not normally distributed. For continuous data, the mean and SD (parametric data) or the median and percentiles (non-parametric data) will be reported. For categorical data, numbers and frequencies will be reported. First, data will be reported for the entire study population. A subgroup analysis will be performed, discriminating between CR or withholding from CR. Differences in outcomes will be analyzed using the unpaired *T*-test in case of normally distributed data or the Mann–Whitney test in case of not normally distributed data. Separate analysis will be performed for average VAS score per patient and average VAS score per day to show both the overall average pain preoperatively and the daily trend towards day of surgery. This will show insight to possible effects on the average caused by patients waiting longer for their surgery. Descriptive analysis will be performed in order to report outcome measures for the total population (main analysis) and (if applicable) the subgroups as mentioned above. For continuous data, the mean and SD (parametric data) or the median and percentiles (non-parametric data) will be reported. For categorical data, numbers and frequencies will be reported. Given the expected low sample size, neither univariate nor multivariable analyses will be done. Trends in PRWE scores will be assessed using generalized linear mixed models calculating the marginal mean differences. Differences in complication rates and re-interventions will be analyzed using the chi-square test of Fisher’s exact test.

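### The sentence barring univariate and multivariable analyses contradicts the mixed model the trial was sized on, and forgoes baseline adjustment for a reason that fails at 120 patients

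*Protocol article*

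**What the plan says.** Statistical methods for primary and secondary outcomes {20a} states: "Given the expected low sample size, neither univariate nor multivariable analyses will be done". For the comparison between arms it says: "Differences in outcomes will be analyzed using the unpaired *T*-test in case of normally distributed data or the Mann–Whitney test". The same section plans generalized linear mixed models for the PRWE.

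Sample size {14}, in the text after Fig. 1, describes the simulation behind the final number: "Linear mixed models were fitted including center as random effect and month and treatment as fixed effects". It says the analysis should allow for season, and that each patient's average VAS will come from a multilevel mixed model with patients nested in centres. Section {20c} names a linear mixed model for missing data. None of these places lists a patient-level baseline covariate.

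On allocation, Implementation {16c} says: "With the cluster randomization, every hospital will know beforehand what intervention to assign". Concealment mechanism {16b} says: "Since this trial will not be blinded, there are no concealment mechanisms". Section {26a} says: "Informed consent will be obtained by the attending physician at the emergency department".

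On the candidate covariate, section {18a} says: "The VAS score prior and after the plaster application will represent their current pain experience".

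**The concern.** There are two problems.

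First, the document gives two incompatible accounts of how the arms will be compared. The 120 evaluable patients were obtained for a model that {20a}, read as written, excludes. The two-group tests contain neither centre nor month, so the power statement does not describe the analysis named in the methods section.

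Second, the physician who takes consent works in a hospital that knows which arm it is currently delivering. Who is approached, and who agrees, can therefore differ between the two periods of a hospital. The within-hospital cross-over balances stable differences between hospitals, but not a change in patient mix between periods. An unadjusted comparison carries any resulting difference in initial pain straight into the primary estimate. In a non-inferiority trial, a shift favouring no reduction makes a false claim of non-inferiority more likely; the opposite shift makes a true one harder to show.

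**Working it through.** **Inputs from the protocol.** Margin 9.7 mm, SD 15 mm, ICC 0.06, two-sided alpha 5% (2.5% one-sided at the margin), power 80%, 120 evaluable and 134 enrolled, monthly inclusions 13, 7, 7, 1, 1, 1 (all {14}); equal allocation ({8}).

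**Assumptions, not in the documents.** Baseline–outcome correlation r of 0.3 to 0.5; baseline imbalance of 5 mm; slope of outcome on baseline of 0.3 to 0.7. The protocol itself says it has no reliable correlation estimate for daily VAS scores.

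**1. The plan's own figures.**
- Dropout: 120 / (1 − 0.10) = 133.3, rounded up to 134. This reproduces.
- Simulation 1: per arm 2 × (1.96 + 0.84)² × 15² / 9.7², rounded up to 38, so 76 in total. A t-based check with the centre effect removed gives power 0.814 at 80 patients, close to the stated 80.
- Simulation 2: the variance under the model with month fixed and centre random, averaged over all 20 ways of giving three of six centres each starting arm, gives power 0.61–0.63 at 60, 0.81–0.83 at 90 and 0.88–0.89 at 120. The range reflects whether SD 15 is read as total or within-centre. This is compatible with a figure of 120 described as rounded up, but the original simulation cannot be rerun.

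**2. Does sample size justify the ban?** Variance inflation from k covariates at 120 patients is about 117 / (117 − k).
- k = 1: 117/116 = 1.009, or 0.9%.
- k = 5: 117/112 = 1.045, or 4.5%.

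The sizing model already estimates month effects at this sample size.

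**3. Precision forgone.** Adjustment multiplies residual variance by 1 − r².
- r = 0.3: factor 0.91, a 9% cut; power under the simulation 2 model 0.90–0.91.
- r = 0.5: factor 0.75, a 25% cut; power 0.94–0.95.

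The starting value is 0.88–0.89, so the planned 80% does not depend on the covariate.

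**4. Effect of an imbalance on the unadjusted test.** With 60 per arm, SE = 15 × √(2/60) = 2.74 mm. Shift = slope × 5 mm. One-sided error at the margin = Φ(−1.96 + shift/SE) if the shift favours no reduction. Power = Φ((9.7 − shift)/SE − 1.96) if it goes the other way.

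| Slope | Shift (mm) | Share of margin | Error if favouring no reduction | Power if against |
|---|---|---|---|---|
| none | 0 | 0% | 2.5% | 94% |
| 0.3 | 1.5 | 15% | 8% | 85% |
| 0.5 | 2.5 | 26% | 15% | 75% |
| 0.7 | 3.5 | 36% | 25% | 62% |

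The 94% is for the simple two-group test with no seasonal effect, so it is not comparable with the 0.88–0.89 in step 3.

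**5. Is the ED VAS a clean baseline?** Section {18a} times it only relative to the plaster. The Abstract gives the order in the reduction arm: "we will randomize between closed reduction followed by plaster casting and only plaster casting". A score taken before plaster could therefore follow reduction in one arm only. Also, {12} starts the outcome average at the ED visit, while {18a} also describes it as starting on day 1, so the score may be part of the outcome.

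**The case against.** A reader might infer that the plan excludes all modelling. The document does not support that: {14}, {20c} and the PRWE sentence in {20a} all plan or presuppose mixed models. Taken literally, the word univariate would even bar the two-group tests in the same paragraph, so the sentence may be aimed only at exploratory regression. This narrows the point to a contradiction, but the contradiction still has to be resolved, and no section supplies a baseline covariate.

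A reader might also infer that selection must favour no reduction. Nothing establishes the direction. The Background calls reduction painful and possibly traumatizing, so patients in most pain could equally decline during reduction periods. That patients themselves know the arm when they consent is likewise not stated; only the hospitals' knowledge is.

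It can further be said that precision is an efficiency preference, since the trial was sized without the covariate; that adjustment cannot repair selective enrolment; and that the protocol already has two safeguards, the within-hospital cross-over and the record of eligible but excluded patients with reasons (Discussion). All of this stands. It limits what adjustment can deliver, but it does not rescue the stated reason for the ban.

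**Conclusion.** The point holds in limited form. The sentence in {20a} conflicts with {14} and {20c}, and its reason fails because one covariate costs about 1% in variance at 120 patients. Forgoing baseline adjustment matters here because recruiters know the allocation and imbalance is possible in either direction.

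The size is illustrative. It rests on an assumed 5 mm imbalance, slopes of 0.3 to 0.7, and the SE of 2.74 mm for an unadjusted comparison of 60 per arm. On those values one-sided error rises from 2.5% to about 8–25%, or power falls from 94% to 85–62%.

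Three stronger conclusions are not supported. The stated 80% power is not put at risk by leaving the covariate out. A pre-treatment VAS cannot be taken as already available in both arms, because its timing is fixed only relative to the cast; if it follows reduction, adjusting for it could remove part of the treatment effect. And covariate adjustment would not make the comparison safe from selective enrolment, since it deals only with imbalance in what was measured.

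**What to change.** - Delete the sentence in {20a}, and make the mixed model of {14} (treatment, month or period, centre) the primary analysis, so that {14}, {20a} and {20c} agree.
- Add the ED VAS as a prespecified fixed covariate, on two conditions to be written into {18a}: it is recorded before any block, reduction or cast in both arms, and it is excluded from the outcome average.
- Tabulate the log of eligible but not enrolled patients by hospital period and arm.
- State that adjustment addresses measured imbalance only and does not remove selective enrolment.

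The cost is model wording and one timing instruction to sites. If the score has so far been taken after reduction in some patients, it cannot serve as a baseline for them, and that should be reported.

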**Discussion:**

If our study shows that patients who did not receive closed reduction experience no significant drawbacks, we might be able to reorganize the initial care for distal radial fractures in the emergency department. If surgery is warranted, the patient can be sent home with a plaster cast to await the call for admission, decreasing the time spend in the emergency room drastically.

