### Objectives {7}

The aim of this multicenter, randomized clinical trial is to determine if CR in patients with a displaced DRF can be safely abandoned before the plaster cast, as a bridge to surgery, is applied.

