### Outcomes {12}

The primary outcome is the average of the pre-operative visual analog scale for pain (VAS) score, reported on a daily basis from the ED visit until surgery.

Secondary outcomes are wrist function measured with the Patient-Rated Wrist Evaluation (PRWE) score after 6 weeks and 3, 6, and 12 months, length of stay in the ED, type and quantity of used pain medication, patient satisfaction, quality of life, and complications. Furthermore, a cost-effectiveness analysis will be performed using the Medical Consumption Questionnaire (iMCQ) and Productivity Cost Questionnaire (iPCQ) [26, 27], and the ability to assess CT scans of unreduced fractures and reduced fractures will be compared.

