## Assignment of interventions: allocation

### Sequence generation {16a}

Randomization at patient level will be challenging because of the 24/7 availability of the ED in all participating hospitals and therefore the 24/7 availability to include possible candidates. To overcome potential protocol violations and unnecessary loss of potential inclusions, randomization will take place as a cluster per hospital with a cross-over point halfway the needed inclusions per hospital (i.e., after 20 inclusions). This means that patients presenting at the same hospital will receive the same intervention, and halfway this will change to the other intervention (CR or withholding from CR). Using a simple script in R statistics, starting treatment will be randomly decided for each hospital, with guarantee that both treatments will occur three times.

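### The safety aim is supported, for complications, only by a test of difference whose non-significance cannot show absence of harm; at assumed rates of 1% to 10% a doubling would usually be missed

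*Protocol article*

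**What the plan says.** - **Aim** (protocol article, Objectives {7}): "to determine if CR in patients with a displaced DRF can be safely abandoned before the plaster cast".
- **Intended reading** (abstract, Discussion): if patients without reduction "experience no significant drawbacks, we might be able to reorganize the initial care for distal radial fractures".
- **Primary outcome** (Outcomes {12}): "The primary outcome is the average of the pre-operative visual analog scale for pain (VAS) score". This is the only outcome with a non-inferiority margin (9.7 mm) and the only one behind the sample size.
- **Complications** are among the secondary outcomes (Outcomes {12}): "type and quantity of used pain medication, patient satisfaction, quality of life, and complications". Section 18a counts everything described in the patient record, and names carpal tunnel syndrome, compartment syndrome, infection, malunion and revision surgery among others. No expected rate is given.
- **Analysis of complications** (section 20a): "Differences in complication rates and re-interventions will be analyzed using the chi-square test", with Fisher's exact test as the alternative. No margin or interval is stated for this comparison.
- **Allocation** (section 16a): "randomization will take place as a cluster per hospital with a cross-over point halfway". Every hospital is therefore meant to contribute to both arms.

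**The concern.** The trial is framed as non-inferiority, and its aim is worded as safety. For pain the method fits the frame: the sample size section judges the upper confidence limit against a margin. For complications it does not: a test of difference asks whether harm has been demonstrated, whereas a safety claim needs to know how much harm has been excluded.

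Pain cannot stand in for this. The abstract gives relief of tension on neurovascular structures as one reason for reducing the fracture, and section 11b allows reduction in the no-reduction arm if neurovascular symptoms develop. Those harms are captured as complications.

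The stakes are practical. Section 6b expects either outcome to lead to a guideline update. If a non-significant complications test is reported beside a positive pain result, readers may take it as evidence of safety when the data could be compatible with a material increase.

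**Working it through.** **Inputs from the protocol article.** Total 134, or 120 after 10% loss, equally divided: 67 or 60 per arm. Margin 9.7 mm, SD 15 mm, two-sided alpha 5%, power 80% (all for pain). The same alpha is assumed for complications.

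**Input not in the protocol.** The complication rate with reduction. It is assumed and varied below.

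**Step 1. The plan's own figure.** A simple non-inferiority formula for means gives n per arm = 2 × (1.96 + 0.84)² × 15² / 9.7² = 37.5, so 38 per arm or 76 in total; the t-based version gives 78. Both are close to the stated 80 for the balanced simulation. The second simulation's 120 was only approximated (power about 87–89% at 120 and about 61% at 60), which is compatible with the stated 120 but not an exact reproduction. Inflation: 120 / 0.9 = 133.3, so 134, as stated. The pain sample size is not in question; it says nothing about complications.

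**Step 2. Power of the stated test.** By exact enumeration, power = sum over all pairs (a, b) of Bin(a; n, p1) × Bin(b; n, p0), counting only pairs with two-sided p ≤ 0.05. The chi-square is without continuity correction. Each range runs from 60 to 67 per arm.

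| Reduction vs no reduction (assumed) | Fisher | Chi-square |
|---|---|---|
| Doubling, 5% vs 10% | 9–11% | 17–20% |
| Doubling, 10% vs 20% | 25–29% | 33–37% |
| Fourfold, 1% vs 4% | 2–3% | 12–15% |
| Fourfold, 2% vs 8% | 15–19% | 31–35% |
| Fourfold, 3% vs 12% | 32–37% | 48–53% |
| Fourfold, 4% vs 16% | 48–55% | 62–68% |
| Fourfold, 5% vs 20% | 63–70% | 73–78% |
| Fourfold, 10% vs 40% | 96–98% | 98–99% |

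For a fourfold rise, power reaches 50% at a rate with reduction of about 3.7–4.1% (Fisher) or 2.8–3.1% (chi-square). A doubling is usually missed at rates from 1% to 10%. At 15% vs 30% with 67 per arm, power is about even (48% Fisher, 55% chi-square).

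**Step 3. What an interval would show.** Newcombe's method combines the Wilson limits of the two arms. For 3/67 the proportion is 0.0448, with Wilson limits 0.0153 and 0.1236. With 3/67 in both arms the difference is 0 and the half-width is √[(0.1236 − 0.0448)² + (0.0448 − 0.0153)²] = 0.084. The 95% interval is −8.4 to +8.4 percentage points, while the test gives p = 1. With 5/67 without reduction and 2/67 with it, Fisher gives p = 0.44 and the interval is −3.9 to +13.6 points. With no events in one arm of 67, the two-sided 95% upper limit for that arm's rate is 1 − 0.025^(1/67) = 5.4%.

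**Step 4. Size needed to exclude an increase.** With true rates equal at p, n per arm = (1.96 + 0.84)² × 2p(1 − p) / d². For p = 5% this gives 299 per arm to exclude a 5-point rise and 75 to exclude a 10-point rise. At this size and an assumed 5% rate, the trial falls somewhat short of 80% power to exclude even 10 points.

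**Step 5. Does pooling hospitals matter?** In a simulated cluster cross-over with assumed hospital effects, Mantel-Haenszel and Fisher had almost the same power: 18.6% vs 18.4% for 2% vs 8%, and 66.8% vs 66.4% for 5% vs 20%. With hospital-by-period effects added, type I error was at most about 5.5% for either.

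**The case against.** The strongest reply is that complications are secondary, that secondary safety outcomes are rarely powered, and that the formal criterion is pain non-inferiority, which must be met whatever the complications test shows. All of that is right. The complications test is not the sole support for the aim: pain, the wrist function score, quality of life, satisfaction and analgesic use all bear on it. It is the only stated comparison of complication rates.

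Three stronger readings are tempting, and the document does not support them.

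- **A formal rule that p above 0.05 means safe.** A reader might infer this from the objective and the abstract together. The abstract's sentence is hedged and does not define significance as statistical. The wording invites the inference but does not state it.
- **A fourfold rise would generally be missed.** This depends on a rate the protocol does not give. It holds for rare single complications, below about 3–4%. It fails at 5% or more, which an all-complications count over one year could reach.
- **Ignoring hospital is what hides harm.** Each hospital crosses over, so stable hospital differences largely cancel, and step 5 shows almost no gain in power from stratifying. Allowing for hospital follows the design but is the lesser part of the remedy.

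It can also be said that frequencies will be reported, so a reader could derive an interval, and that interval format is commonly left to the analysis plan. That has force against a complaint of omission. The point here is different: the method that is stated answers a different question from the stated aim.

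**Conclusion.** The point holds. The aim is worded as safety, the abstract ties reorganised care to the absence of significant drawbacks, and the stated comparison of complication rates is a test of difference that would probably be non-significant even if complications doubled. Its power for a doubling is 9–20% at an assumed 5% and 25–37% at an assumed 10%, across both tests and 60 to 67 per arm. The assumptions are the baseline rate, two-sided 5% for this test, and independent patients. The design itself is sound on this point, and pain non-inferiority is unaffected. This is a should-change matter of analysis and wording.

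**What to change.** 1. **Section 20a:** make the risk difference (no reduction minus reduction) with its 95% confidence interval the basis of the safety statement, in place of the chi-square or Fisher test. Allow for hospital, to follow the design. Report it for all complications and for neurovascular complications.
2. **Objectives {7} and the abstract's discussion:** limit the confirmatory conclusion to pre-operative pain being non-inferior within 9.7 mm. Instead of referring to the absence of significant drawbacks, state the largest increase in complications that the data exclude, which is the upper limit of that interval.

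The cost is a revision of the analysis text and the wording of the conclusion, with no extra patients or data. The drawbacks are a more modest safety claim and sparse strata: the sample size section assumes one inclusion a month at each of three hospitals, so the stratified estimate will draw little from them.
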